| – Outcome               | Radiation dose/time                                                                                                                   |  |
| – Timepoint             | Operation day                                                                                                                         |  |
| Secondary Outcome 1     |                                                                                                                                       |  |
| – Outcome               | Clinical performance of instrumentation technique                                                                                     |  |
| – Timepoint             | Operation day                                                                                                                         |  |
| Secondary Outcome 2     |                                                                                                                                       |  |
| – Outcome               | Hospital days                                                                                                                         |  |
| – Timepoint             | after discharge                                                                                                                       |  |
| 11. Publication         |                                                                                                                                       |  |
| Publication             | 0                                                                                                                                     |  |

<[https://cris.nih.go.kr/cris/search/search\\_result\\_st01\\_en.jsp?seq=4637&type=my](https://cris.nih.go.kr/cris/search/search_result_st01_en.jsp?seq=4637&type=my)>

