| Lay Summary             | 
To quantify potential short- and long-term benefits of robotically-guided minimally invasive spine surgery (MIS) in instrumentation of degenerative thoracic, lumbar or lumbosacral spine disease in adult patients, in comparison to instrumentation in a matching cohort of control patients performed using conventional fluoroscopic-assisted technique.
 
It is hypothesized that use of robotic guidance during spinal instrumentation will have numerous short- and long-term benefits to both patient and surgeon, relative to image-guided MIS techniques. Expected benefits include improved implant accuracy, lower intraoperative or perioperative complications including reduced operation time and blood loss, lower incidence of procedure-related adverse events (e.g., new neurological deficit, implant-related durotomies, implant misplacement), lower reoperation rates, lower incidence of implant failure (e.g., screw
 |

pullout), improved surgical outcomes, a higher ratio of executed:planned instruments, fewer "abandoned" screws.

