| Intervention Description |                    | Robot group : Patients will be selected to participate in the study according to the inclusion/exclusion criteria listed below. Patients will be randomly selected in the robotic surgery arm.
Fluoroscope group : Randomly selected patients will participate in the control arm only. Surgeons comfortable enough with both surgical techniques will randomize their first 60 patients (1:1 ratio, 30 patients to each study arm). In either arm, patients will undergo the surgical intervention according to standard hospital care and surgical techniques – with or without robotic guidance, according to the study arm. |
| Number of Arms           |                    | 2                                                                                                                                                                                                                                                                                                                                                                                                                                                                                                                                                                                                                                  |
| Arm 1                    | Arm Label          | Robot group                                                                                                                                                                                                                                                                                                                                                                                                                                                                                                                                                                                                                        |

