| Exclusion Criteria            |                 | 1. Infection or malignancy
2. Primary abnormalities of bones (e.g. osteogenesis imperfecta, congenital or idiopathic spinal deformities)
3. Primary muscle diseases, such as muscular dystrophy
4. Neurologic diseases (e.g. Charcot-Marie Tooth, Guillain-Barre syndrome, cerebral palsy, spina bifida, or neurofibroma)
5. Spinal cord abnormalities with any neurologic symptoms or signs
6. Spinal cord lesions requiring neurosurgical interventions, such as hydromyelia
7. Paraplegia
8. Patients requiring anterior release or instrumentation
9. Any other significant disease or disorder which, in the opinion of the Investigator, may either put the participants at risk because of participation in the study, or may influence the result of the study.
10. Patient cannot follow study protocol, for any reason
11. Patient (or legal guardian, when applicable) cannot or will not sign informed consent                                                                                                                                                                                                                                                 |
| Statistical considerations    |                 | Statistical analysis
Descriptive statistics of demographic data will be presented for the entire study population.

Statistics will be provided also for all the primary and secondary endpoints, including at a minimum mean and standard deviation, and compared between robotic surgery and control arms. Strong trends that are identified in the data will also be analyzed for statistical significance and power.

Data analysis
The data will be aggregated into two groups (robotic surgery and fluoroscopic control arms) by the principal investigator or a designee, and de-identified as to patient information as well as surgical technique (with/without robotic guidance) information. The de-identified data will be analyzed.

Descriptive statistics will be provided for all demographic data and relevant endpoints. The means and standard deviations (SD) of quantitative variables will be calculated and compared between the two arms. Paired t-tests or signed rank tests for two rank tests for paired observations will be applied to determine the statistical significance of the changes measured.

Alpha is defined as 5%. |

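### The only significance tests named are paired tests of undefined changes, so no test is specified for the randomised comparison of two independent arms

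*Supplement*

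**What the plan says.** The Supplement is a trial registration record with its own statistical section (section 9, Statistical considerations). On the comparison of arms it makes two promises: endpoints will be "compared between robotic surgery and control arms", and "The means and standard deviations (SD) of quantitative variables will be calculated and compared between the two arms". Neither names a test or an effect measure. The one sentence that names tests reads "Paired t-tests or signed rank tests for two rank tests for paired observations will be applied", and it ends by giving their purpose: "to determine the statistical significance of the changes measured". The changes are not defined. A further sentence adds "Strong trends that are identified in the data will also be analyzed for statistical significance and power", again with no test. Alpha is set at 5%, without saying whether it is one- or two-sided.

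Section 8 (Study Design) gives a parallel model with randomised allocation, and says that surgeons "will randomize their first 60 patients (1:1 ratio, 30 patients to each study arm"). The Lay Summary in section 7 describes the comparison differently: "in comparison to instrumentation in a matching cohort of control patients performed using conventional fluoroscopic-assisted technique". No matching variables and no rule for forming pairs appear anywhere.

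**The concern.** A paired test needs two linked observations per unit. In a parallel trial the robot and fluoroscopy patients are different people, so the comparison that randomisation protects calls for an independent-groups method. None is named for any outcome type: continuous, ordinal or binary.

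Two things are at stake. First, within-arm p-values may stand in for a comparison of arms, so that improvement significant with the robot but not with fluoroscopy is reported as a benefit of the robot. Second, with four primary outcomes and no between-arm test fixed, the choice of test stays open until the data have been seen. The sentence about strong trends points the same way.

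**Working it through.** **Inputs.** From the Supplement: 30 patients per arm, 1:1, parallel, alpha 5%. Assumed: a two-sided test, normal data, and the standardised effects below. The record gives no effect size, SD, event rate or power, so its target of 60 cannot be reproduced. The point concerns the type of test, not the sample size.

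**Reading 1: paired within patient (after versus before), separately in each arm.** Let δ be the true mean change divided by the SD of the change, equal in both arms. Each paired t-test has 29 df, critical value 2.045 and noncentrality δ√30. Let p be its power. As the arms are independent, the chance that exactly one is significant is 2p(1−p).

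| δ (assumed) | δ√30 | p | 2p(1−p) |
|---|---|---|---|
| 0.2 | 1.10 | 0.185 | 0.30 |
| 0.3 | 1.64 | 0.355 | 0.46 |
| 0.36 | 1.97 | 0.479 | 0.50 |
| 0.5 | 2.74 | 0.754 | 0.37 |
| 0.8 | 4.38 | 0.988 | 0.02 |

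For example, at δ = 0.2: 2 × 0.185 × 0.815 = 0.30. The true difference between arms is zero in every row. The value 0.36 lies close to the maximum of 2p(1−p), which is 0.50 at p = 0.5. At 0.8 SD both arms are nearly always significant; discordance is then rare, but the arms have still not been compared.

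**Reading 2: robot patients paired with fluoroscopy patients.** With arbitrary pairs the true correlation is zero, so the noncentrality is d√30/√2 = d√15, the same as for the independent test. Only the degrees of freedom differ: 29 (critical value 2.045) against 58 (2.002).

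- Power at d = 0.5 (noncentrality 1.94): 46.5% paired, 47.8% independent.
- Power at d = 0.8: 85.0% paired, 86.1% independent.
- Simulated type I error of the arbitrary paired test: 4.9%.
- Re-ordering one arm's list and repeating the paired test, at d = 0.5: significance changes in about 8% of simulated trials.
- In one simulated data set of 30 versus 30, the independent test gave p = 0.004, while 5,000 random pairings gave p from 0.00007 to 0.024.

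Pairing across arms also cannot use every patient if the numbers analysed differ between arms.

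**Which outcomes have a before/after pair?** Section 7 (Primary Endpoints) and section 10 (Outcome Measures) give:

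- VAS, ODI and SF-36: a within-patient change is possible if a preoperative value is collected.
- Screw accuracy: a grade from postoperative CT only, so no pair. It is ordinal, and a patient normally contributes several screws.
- Complications and reoperation: events during follow-up, so no pair. They are binary.
- Radiation: operation day only, so no before/after pair.

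**The case against.** The strongest reply is that the sentence limits itself to paired observations and to changes measured. Its natural meaning is then before/after change in the questionnaires, where a paired test is correct. That stands: under this reading the tests are valid, but for a different question from the one the trial asks.

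A reader might go further and infer that the arms will never be compared, or that they will certainly be mis-analysed. The documents do not support this. A between-arm comparison is promised twice, and an unnamed suitable test may be intended. What the text supports is that no between-arm test is specified. Nor does any sentence say that within-arm p-values will be set against each other, so the 30% to 50% figures describe a risk and not a planned analysis.

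It can also be said that no separate analysis plan is shown, and that tests for each endpoint are commonly left to one. Missing detail alone would not be a finding. Here, however, the record has a statistical section, and the one testing rule it states does not fit the randomised comparison.

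Three smaller points stand. Arbitrary pairing does little harm to error rates. Dosimeters worn above and under the protectors do give a natural pair of readings, though it measures shielding and not robot against fluoroscopy. And a link between the matching-cohort phrase and the paired tests is conjecture; the phrase simply does not describe this design.

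**Conclusion.** Wrong as written. The named tests are either valid for within-patient questionnaire change and silent on robot versus fluoroscopy, or they rest on pairs that the design does not contain. Under the first reading, discordant within-arm results arise in 30% to 50% of trials with no true arm difference at assumed changes of 0.2 to 0.5 SD, falling to 2% at 0.8 SD. Under the second, about 8% of trials change significance on re-ordering at an assumed 0.5 SD difference, while the loss of power is about 1 point and type I error is near nominal. These sizes rest on assumed effects, normality and two-sided testing.

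The conclusion itself does not depend on them. It rests on independent arms, undefined pairs, and no applicable test for the ordinal and binary primary outcomes.

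**What to change.** Before outcomes are analysed by arm, replace the paired-test sentence with independent-group methods by randomised arm:

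- Operation time, blood loss and radiation: Welch t-test or Wilcoxon rank-sum test.
- VAS, ODI and SF-36: a between-arm comparison, ideally ANCOVA adjusted for the baseline value if it is collected.
- Complications and reoperation: Fisher exact test, or risk difference with a 95% confidence interval.
- Gertzbein–Robbins screw grades: an ordinal or binary analysis that allows for clustering of screws within patient. Standard two-sample tests applied to individual screws would not do this.

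Keep paired tests only as descriptive within-arm summaries, and say which changes they concern. State whether the 5% level is two-sided. Reconcile the matching-cohort wording in the Lay Summary with the randomised design.

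The cost is a revision of wording in the statistical section and the Lay Summary; no further patients or measurements are needed.
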